## Abstract

Ulcerative colitis, characterized by its relapsing and remissive nature, negatively affects perception, body image, and overall quality of life. The associated financial burden underscores the need for alternative treatment approaches with fewer side effects, alongside pharmaceutical interventions. Montmorency tart cherries, rich in anthocyanins, have emerged as a potential natural anti-inflammatory agent for ulcerative colitis. This manuscript outlines the study protocol for a randomized placebo-controlled trial investigating the effects of Montmorency tart cherry in individuals with ulcerative colitis. The trial aims to recruit 40 participants with mild to moderate disease activity randomly assign them to either a Montmorency tart cherry or placebo group. The intervention will span 6 weeks, with baseline and 6-week assessments. The primary outcome measure is the Inflammatory Bowel Disease Quality of Life Questionnaire. Secondary outcomes include other health-related questionnaires and biological indices. Statistical analysis will adhere to an intention-to-treat approach using linear mixed effect models. Ethical approval has been obtained from the University of Hertfordshire (cLMS/SF/UH/05240), and the trial has been registered as a clinical trial (NCT05486507). The trial findings will be disseminated through a peer-reviewed publication in a scientific journal.

## 1. Introduction

Ulcerative colitis (UC) is an inflammatory bowel disease that is denoted by acute, non-infectious relapsing and remitting inflammation of the intestinal mucosa [1]. In the United States, there is a prevalence as high as 500 per 100,000 individuals [2], with similar incidence rates noted in the United Kingdom [3] and the prevalence of UC is increasing in many other parts of the developed world [4]. The rising frequency, high morbidity, and fiscal burden of UC are a significant clinical concern. The average direct cost of UC has been estimated to be > USD 3500 per patient, much of which is attributed to medications [5], with one UK drug estimated to cost GBP 400 million per year [6]. Indeed, recent healthcare economic analyses have shown that pharmaceutical agents utilized for UC represent some of the most expensive medications within the US health service [7]. Therefore, UC requires additional financial resources and infrastructure for efficient, long-term disease management [4]. The direct fiscal impact of this condition in the United Kingdom alone exceeds GBP 720 million per annum [8], with prevalence increasing by 0.3% per year in Europe [9].

UC commonly emerges during early adulthood, and its fluctuating and recurring nature can significantly impact patients’ overall health perception, body image, and quality of life [10]. This effect is particularly notable in individuals experiencing active disease, as they tend to report a diminished quality of life compared to those in remission [10]. Patients with UC often exhibit higher levels of psychological distress, anxiety, heightened sensitivity to bodily sensations, and perceive lower levels of social support when compared to healthy individuals [11]. Various factors contribute to a reduced health-related quality of life, including diminished participation in social activities and the impact on relationships with friends, family members, and romantic partners [12]. Furthermore, UC is associated with decreased participation in the labour force, which further amplifies the economic consequences of the condition [13].

The primary objective of treatment for UC is to suppress inflammation [14]. For individuals with mild to moderate disease symptoms, 5-aminosalicylic acid is commonly prescribed [15]. However, the response rates to these agents are typically around 40–50% [16] and can lead to substantial side effects such as hepatitis, pancreatitis, nephritis/nephrotoxicity, and pulmonary dysfunction, and in some cases, they may even worsen the severity of the disease [16]. In cases of moderate to severe UC, corticosteroids and immunosuppressive medicines are often utilized [17]. However, the improvement achieved with this approach is usually protracted and also comes with the risk of significant side effects, including an increased susceptibility to non-Hodgkin’s lymphoma, allergic reactions, hepatic/pancreatic inflammation, infection, tuberculosis, and viral hepatitis [18].

UC is associated with excessive reactive oxygen species levels, generated by activated macrophages and neutrophils within the inflamed intestine [19], as well as imbalances of oxidative stress [20] and diminished capacity of the antioxidant defense system within the intestines [21]. Alternative treatment modalities are increasingly being sought for the management of UC [22]. Recently, more emphasis on dietary therapies have been advocated for UC, as it is thought to alter the composition of gut microbiota [23]. It has been further hypothesized owing to their potential to attenuate inflammation of the gastrointestinal tract, that natural antioxidative and anti-inflammatory agents might be beneficial and offer a treatment approach with fewer side effects compared to pharmaceutical interventions, and recent clinical and animal studies support this notion [14,24]. Anthocyanins form a crucial sub-class of dietary flavonoids and are abundant in dark fruits where they provide the deep colouring in these fruit groups [25]. Importantly, it has been shown that anthocyanins mediate significant antioxidant properties and have been demonstrated to improve and prevent heart disease and certain cancer modalities, in addition to inflammatory pathologies [26], although research concerning their efficacy in UC remains in its infancy.

Animal models show that anthocyanin-rich bilberry ingestion attenuates the severity of disease activity and reduces pro-inflammatory cytokine serum levels [27]. Two subsequent interventions in human participants showed firstly that 6 weeks of bilberry supplementation significantly improved endoscopic disease activity and faecal calprotectin levels [14] and reduced amounts of the pro-inflammatory cytokines IFN-γ and TNF-α from colon biopsies as well as reduced serum levels of TNF-α and MCP-1 [26]. Montmorency tart cherries are considered a rich source of anthocyanins [28], and supplementation has been demonstrated to increase Bacteroides in the gut [29], known to decrease colon inflammation in IBD [30]. Biochemical investigations have shown that the anthocyanin content of Montmorency tart cherries is greater than the majority of dark fruits [28], which has led to the idea that their clinical efficacy may be greater than those observed previously using bilberry supplementation in patients with UC.

### 1.1. Rationale

There are no placebo-controlled, randomized trials examining the efficacy of Montmorency tart cherry in patients with UC. Our research [31] has revealed a strong willingness to take Montmorency tart cherry supplementation in patients with UC, demonstrating a high-level of patient engagement for a randomized clinical trial involving Montmorency tart cherry supplementation. Therefore, further exploration of the health benefits of tart cherries in patients with UC may be of both practical and clinical relevance.

### 1.2. Aims and Objectives

The objective of this trial, is to assess the impact of twice daily Montmorency tart cherry supplementation, on various health indicators in patients with UC, in comparison to the placebo. The primary aim of this randomized trial is to investigate the effects of Montmorency tart cherry supplementation on self-reported quality of life, specifically using the Inflammatory Bowel Disease Quality of Life Questionnaire, in comparison to the placebo group. Secondary objectives involve evaluating whether tart cherry supplementation has any influence on other health-related questionnaires and biological indices.

## 2. Experimental Design

### 2.1. Study Design and Setting

This study adheres to the latest guidelines for reporting parallel-group randomized trials [32]. The University of Hertfordshire in Hertfordshire, South England, will serve as the location for the trial. The research follows a 6-week parallel design, incorporating randomized allocation with a placebo control (Figure 1). Upon confirming a participant’s suitability and enrollment, a computer program (random assignment software) will individually assign them to one of two groups for the duration of 6 weeks: (1) Montmorency tart cherry supplement or (2) placebo. The primary and secondary outcome variables will be assessed at baseline and after 6 weeks, as described below. Consistent with previous studies on UC management, the primary outcome will be on examining the differences between groups in the Inflammatory Bowel Disease Quality of Life Questionnaire questionnaire between the two groups. Secondary outcomes will be other health-related questionnaires and biological indices.

### 2.2. Inclusion Criteria

To be eligible for inclusion in this study, participants must meet the following criteria: (1) have a confirmed diagnosis of UC for a minimum of 6 months, (2) exhibit mild to moderate disease activity at the time of enrollment, (3) fall within the age range of 18 to 65 years, and (4) have maintained consistent use of medication for a minimum of 3 months. The aforementioned inclusion criteria were collectively adopted based on previous randomized trials in patients with UC [33,34]. Mild–moderate disease activity will be given a Mayo Clinic Score between 3–10, in accordance with the British Society of Gastroenterology consensus guidelines [35].

### 2.3. Exclusion Criteria

Exclusion criteria for this trial include the presence of diabetes, HIV, rheumatoid arthritis, or any other autoimmune disease, as well as hepatitis B and C infections. Additionally, individuals with abscesses, unstable medical conditions that may hinder their ability to complete the study or known food allergies to cherries will also be excluded from participation.

### 2.4. Sample Size

There has yet to be any investigation examining the efficacy of Montmorency tart cherry in patients with UC. Therefore, a pragmatic a priori sample size calculation was undertaken based on a previous trial examining the effects of bilberry supplementation on UC health-related quality of life change scores quantified using the Short Inflammatory Bowel Disease Questionnaire [14]. Considering an expected attrition rate of 20%, this revealed that 20 participants would be necessary in each trial arm, with a total N of 40, to achieve *α* = 5% and *β* = 0.80, enabling an increase in health-related quality of life of 6.5 points to be detected.

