#### 3.2.1. Questionnaires

The primary outcome measure for this study will be the Inflammatory Bowel Disease Quality of Life Questionnaire. Secondary questionnaires will include the simple clinical colitis activity index (SCCAI), IBD Fatigue Scale, International Physical Activity Questionnaire—Short Form (IPAQ-SF), and the Hospital Anxiety and Depression Scale. The Inflammatory Bowel Disease Quality of Life Questionnaire is a widely used and validated instrument, specifically designed for patients with IBD [41,42]. It consists of 32 items scored on a 7-point Likert scale, with higher scores indicating better IBD-related quality of life based on a range of 32–224. The questionnaire assesses four dimensions: bowel symptoms, systemic symptoms, emotional well-being, and social functioning. The simple clinical colitis activity index (SCCAI) is a validated, symptom-based index comprising six items. Scores on this index range from 0 to 19, with higher scores indicating more severe symptoms [43]. The IBD Fatigue Scale is an IBD-specific tool that evaluates fatigue in individuals with IBD [44]. It consists of two components: one estimates the level of fatigue using five questions, and the other measures the impact of fatigue on quality of life using 30 questions. Scores are calculated on a 0–4 Likert scale, with a maximum score of 120 and higher scores indicating higher levels of fatigue and greater impact on quality of life. The International Physical Activity Questionnaire—Short Form (IPAQ-SF) is a validated questionnaire consisting of nine items. It assesses physical activity across four intensity levels: vigorous-intensity activity, moderate-intensity activity, walking, and sitting. Energy expenditure is calculated in metabolic equivalents per week [45]. The Hospital Anxiety and Depression Scale is a validated 14-question scale used to assess symptoms of anxiety and depression. It comprises separate sections for depression (7 questions) and anxiety (7 questions), with scores ranging from 0 to 21 for each section. Higher scores indicate greater levels of depression or anxiety [46].

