### 3.4. Statistical Analysis

Continuous experimental variables will be presented as mean values along with their corresponding standard deviations. To compare participant characteristics at baseline, as well as compliance levels, experimental anthocyanin intake, experimental energy intake, and experimental sugars (g/day) between the trial arms, between-group linear mixed effects models will be utilized. In these models, the group will be treated as a fixed factor, and random intercepts will be included for participants.

All analyses of the intervention-based data will follow an intention-to-treat approach. To determine the effects of the intervention on all of the outcome measures, differences in the changes from baseline to 6 weeks between the two trial arms will be examined using linear mixed-effects models with a group modelled as a fixed factor and random intercepts by participants adopted. For linear mixed models, the mean difference between groups in changes from baseline to 6 weeks (*b*) and 95% confidence intervals of the difference will be presented. Effect sizes were calculated for the changes from baseline to 6 weeks between the two groups, using Cohen’s *d*, in accordance with McGough & Faraone [51]. Cohen’s d values will be interpreted as 0.2 = small, 0.5 = medium, and 0.8 = large [52]. The efficacy of blinding will be assessed using a one-way chi-square (*Χ*^2^) goodness-of-fit test. Chi-square analyses will be calculated using Monte-Carlo simulation to determine probability values. All statistical analyses will be performed using SPSS v28 (IBM Inc., SPSS, Chicago, IL, USA), and statistical significance will be considered at a *p* ≤ 0.05 level.

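### The sample-size paragraph gives β = 0.80, a type II error of 80%, where power of 0.80 (β = 0.20) was most likely meant

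*Protocol article*

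**What the plan says.** Section 2.4 (Sample Size) of the protocol article holds the whole calculation. It starts from an earlier bilberry trial's "quality of life change scores quantified using the Short Inflammatory Bowel Disease Questionnaire". It allows for dropout ("Considering an expected attrition rate of 20" per cent) and concludes that "20 participants would be necessary in each trial arm", "with a total N of 40, to achieve *α* = 5% and *β* = 0.80". The target is given as "enabling an increase in health-related quality of life of 6.5 points to be detected".

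Section 3.4 (Statistical Analysis) gives the significance level ("statistical significance will be considered at a *p* ≤ 0.05 level") and says that the between-group difference in change will be reported with a 95% confidence interval. It does not mention power. Section 3.2.1 names the primary outcome: "The primary outcome measure for this study will be the Inflammatory Bowel Disease Quality of Life Questionnaire", a 32-item instrument scored from 32 to 224.

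**The concern.** α and β stand side by side as the properties that the sample size secures. In that pairing α is the type I error rate and β the type II error rate, the chance of missing a true effect of the target size. Taken at face value, the sentence describes a design that would miss a 6.5-point effect four times in five.

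No other section states a power, defines β as power, or otherwise corrects the figure. Anyone who takes the planned power from this article, such as an ethics committee, a journal reader or a systematic reviewer, must either record 20% or guess that the symbol is wrong. What is at stake is the accuracy of a stated design figure. The conduct of the trial is not affected.

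**Working it through.** **Inputs**
- α = 0.05, printed β = 0.80, difference 6.5 points, 20 per arm, attrition 20%: all from Section 2.4.
- Sidedness: not stated in Section 2.4. Two-sided is assumed, in line with the 95% confidence interval in Section 3.4.
- SD of the change score: not printed.

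**Step 1. Definition.** Power = 1 − β = 1 − 0.80 = 0.20. This depends on neither the sidedness nor the SD.

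**Step 2. Attrition.** 20 × (1 − 0.20) = 16 evaluable per arm. In reverse, 16 / 0.80 = 20 per arm and 40 in total. The printed dropout and N agree with each other.

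**Step 3. Can N = 40 be reproduced?** For two means, n per arm = 2(z₁₋α/₂ + z_power)² SD² / δ². The SD is missing, so N cannot be derived directly. The formula can be solved for the SD that 16 per arm implies:

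SD = δ √(n/2) / (z₁₋α/₂ + z_power), where δ √(n/2) = 6.5 × √8 = 18.385.

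- Power 0.80: 18.385 / (1.960 + 0.842) = 6.56, a standardised difference of 6.5 / 6.56 = 0.99.
- Power 0.20: 18.385 / (1.960 − 0.842) = 16.44, a standardised difference of 0.40.

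**Step 4. The same with the noncentral t distribution (30 degrees of freedom, two-sided 5%).**

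| Reading | Power | Standardised difference | Implied SD |
|---|---|---|---|
| 0.80 is the power | 0.80 | 1.024 | 6.35 |
| 0.80 is β | 0.20 | 0.407 | 16.0 |

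With a one-sided 5% test the implied SDs are about 7.2 (power 0.80) and 22.4 (power 0.20).

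**Step 5. How far apart are the readings?** At a fixed SD and difference, 80% power needs (1.960 + 0.842)² / (1.960 − 0.842)² ≈ 6.3 times the participants that 20% power needs.

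**Result.** Each reading fits the printed α, N and 6.5 points for some SD. The arithmetic shows that the label matters, but it cannot show which value was used.

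**The case against.** The best reply is that this is plainly a slip in notation. Section 2.4 presents the sample as what is needed for a 6.5-point increase to be detectable, and nobody recruits in order to have an 80% chance of missing an effect. On that view a reader will take 0.80 as power, and nothing in the design is at fault. Most of this stands and it fixes the weight of the point. It does not make the printed figure correct, and without an SD the intended value has to be inferred from convention.

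Three stronger readings are tempting, and the article supports none of them.

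- **The trial really has 20% power, or N = 40 is wrong.** Actual power depends on N, the true difference and the true variability, and a mislabelled symbol changes none of these. If the SD in the calculation was near 6.4 to 6.6 (two-sided), 20 per arm is what 80% power requires. Working out that 20% power would need only a handful per arm adds no evidence, because the standardised difference used for that already assumes 80% power at 16 per arm.
- **A null result would be uninterpretable.** Section 3.4 commits to a 95% confidence interval for the difference in change. That interval will show which effects the data exclude, whatever β was printed at the planning stage.
- **The wrong β is what stops the sizing from being checked.** The obstacle is the unprinted SD, and it remains after β is corrected. A condensed article may leave the SD to the full protocol, so its absence is not raised here as a fault.

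**Conclusion.** The figure is wrong as printed. β = 0.80 means a power of 20%, and this is the article's only power statement. It is most likely a slip for power = 0.80. The 60-point gap (0.80 − 0.20) separates two readings of a label and is not a demonstrated loss of power.

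The definition needs no assumption. The implied SDs (about 6.35 against about 16.0) rest on 16 evaluable per arm and a two-sided 5% two-sample t-test.

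A corrected power statement would also have a limit that should be made visible. The calculation used Short IBDQ change scores, so 80% power would be established for that measure and not automatically for the 32-item primary questionnaire. That is a separate matter, but the corrected sentence should not hide it. Overall this is a minor correction to a stated figure.

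**What to change.** Check the original calculation. If 0.80 was the power, replace the printed β in Section 2.4 with: power (1 − β) = 0.80, i.e. β = 0.20. In the same sentence:

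- say that it applies to 16 evaluable participants per arm (20 less 20% attrition);
- give the sidedness of the 5% test and the change-score SD used, so that N can be reproduced;
- say that the calculation was made on Short IBDQ change scores and not on the 32-item primary questionnaire.

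If the calculation was in fact run with β = 0.80, state the power as 20%.

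The cost is one corrected figure and a clarifying sentence, with no change to enrolment or analysis.

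### The 6.5-point detectable difference in section 2.4 comes from the Short IBDQ, not the 32-item IBDQ that is the primary outcome, and no SD or conversion supports it on that scale

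*Protocol article*

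**What the plan says.** Section 2.4 (Sample Size) explains that no tart cherry trial in ulcerative colitis exists, so a proxy was used: a bilberry trial's "health-related quality of life change scores quantified using the Short Inflammatory Bowel Disease Questionnaire". Allowing for 20% attrition, it arrives at 20 per arm and 40 in total. The error rates are put as "to achieve *α* = 5% and *β* = 0.80". What this sample is said to deliver is a design "enabling an increase in health-related quality of life of 6.5 points to be detected". The scale of the 6.5 points is not named, and no SD is given.

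Section 3.2.1 (Questionnaires) states: "The primary outcome measure for this study will be the Inflammatory Bowel Disease Quality of Life Questionnaire". Of that instrument it says: "It consists of 32 items scored on a 7-point Likert scale", with a range of 32 to 224. The Abstract and sections 1.2 and 2.1 name the same primary outcome. The Short IBDQ is not among the instruments listed in section 3.2.1.

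Section 3.4 (Statistical Analysis) compares the arms on change from baseline to 6 weeks, with 95% confidence intervals, and "statistical significance will be considered at a *p* ≤ 0.05 level".

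**The concern.** A detectable difference in raw points means something only on the scale on which it was derived. The article's one sample-size statement gives a figure in points from calculations on one questionnaire, while the trial tests another whose scores span 192 points. A short form has fewer items, so neither a 6.5-point change nor its SD can be assumed to carry over unchanged.

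Section 2.4 is the only justification of N=40. A reader who takes it at face value will believe that a 6.5-point between-arm difference on the 32–224 scale is tested with 80% power, and may read a non-significant result as evidence against an effect of that size.

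The same sentence sets β at 0.80. β is the type II error rate, so read literally this is 20% power. It is evidently a notation slip for power of 0.80.

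**Working it through.** **Inputs**
- From section 2.4: 20 per arm, 20% attrition, α = 5%, power 80% (reading the β statement as power), difference 6.5 points.
- From section 3.2.1: IBDQ range 32–224, a span of 224 − 32 = 192 points.
- From section 3.4: the quantity tested is the between-arm difference in change.
- Assumed: a two-sided test. Section 2.4 does not say, but section 3.4 plans 95% confidence intervals and a 0.05 threshold.
- Not in the article: the SD of change on either questionnaire, and the item count or range of the short form.

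**Step 1: the plan's own figure.** Evaluable per arm = 20 × (1 − 0.20) = 16, and 16 / 0.80 = 20. The attrition arithmetic is consistent. The 20 per arm cannot be reproduced independently because no SD is stated, so I solved for the SD that it implies.

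**Step 2: the implied SD.** For two arms of n, the difference detectable with 80% power is Δ = d × SD, where d is the standardised difference.
- Normal approximation: d = (1.960 + 0.842) × √(2/16) = 0.991, so SD = 6.5 / 0.991 = 6.56.
- Noncentral t with 30 degrees of freedom: d = 1.024, so SD = 6.5 / 1.024 = 6.35.
- Variants (noncentral t): a one-sided test with 16 per arm implies SD 7.23; a two-sided test with all 20 analysed implies SD 7.15 (d = 0.909).

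So the claim is true on the IBDQ only if the SD of IBDQ change is about 6.4 points, or 6.35 / 192 = 3.3% of the span. The variants move this only to about 7.2.

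**Step 3: power for 6.5 points on the IBDQ.** As no IBDQ SD is given, I varied it. Noncentral t, two-sided 5%, 16 per arm; noncentrality = 6.5 / (SD × √(2/16)); detectable difference = 1.024 × SD.

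| Assumed SD of IBDQ change | Power for 6.5 points | Difference detectable with 80% power |
|---|---|---|
| 6.35 | 80% | 6.5 |
| 10 | 43% | 10.2 |
| 15 | 22% | 15.4 |
| 20 | 14% | 20.5 |
| 25 | 11% | 25.6 |
| 30 | 9% | 30.7 |

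**Step 4: what if the standardised effect carries over?** Suppose scores scale with the number of 7-point items and, purely as an assumption, the short form has 10 items. The SD becomes 6.35 × 32/10 = 20.3 and the effect becomes 6.5 × 32/10 = 20.8. Then d = 20.8 / 20.3 = 1.02 and power is still about 80%, for 20.8 IBDQ points. With 12 or 16 items the corresponding differences are 17.3 and 13.0 points, again with about 80% power.

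**The case against.** The strongest reply is that rescaling must be applied to the effect as well as to the SD. Step 4 does this, and power for the planned standardised effect does not fall. A reader might infer from the table in Step 3 that the trial is underpowered or that N must rise. The documents do not support that: the low percentages are for 6.5 raw IBDQ points, which at SDs of 10 to 30 is a standardised effect of 0.65 to 0.22, well below the roughly 1.0 implied by the design. This part of the reply stands, and it limits the point to the stated difference.

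It is also fair that section 2.4 calls the calculation pragmatic, and that its link between the 6.5 points and the short form is a close inference from the wording, not a labelled unit. Being pragmatic explains borrowing from a bilberry trial. It does not explain leaving the scale of the target unstated when the analysed instrument is different.

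The confidence interval promised in section 3.4 will show which differences remain compatible with the data, so a null result would not inevitably be misread. That lessens the consequence but leaves the sample-size statement unsupported.

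A reader might also take the word increase in section 2.4 to mean a within-arm gain. The surrounding references to change scores and to trial arms fit a between-arm comparison, so I do not press this. Nor does the β slip suggest that the trial was really planned with 20% power.

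**Conclusion.** The point holds as a mismatch of instruments. The mismatch itself is plain in the text and needs no assumption: the calculation rests on the Short IBDQ, the test is on the 32-item IBDQ, and nothing connects the two. The claim of 80% power for 6.5 points is therefore unsupported for the primary outcome, and is correct there only if the IBDQ change SD is about 6.4 points.

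The size of the discrepancy depends on an SD that the article does not supply. Over assumed SDs of 10 to 30, power for 6.5 points is about 43% to 9%, and the detectable difference is about 10 to 31 points. These figures assume a two-sided 5% comparison of mean change with 16 evaluable per arm. They do not demonstrate a loss of power for the planned standardised effect. What is wrong is the detectable difference as stated, together with the β notation.

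**What to change.** Rewrite section 2.4 on the 32–224 IBDQ scale:
- State the assumed SD of IBDQ change and its source.
- State the between-arm difference in change detectable with 80% power and 16 evaluable per arm, about 1.02 times that SD. If the argument is that the standardised effect from the bilberry trial carries over, say so and give the matching IBDQ difference.
- Remove the 6.5-point claim for the primary outcome, or label it explicitly as Short IBDQ points.
- Write power = 0.80 (β = 0.20), and state that the test is two-sided if that is intended.

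Keep N=40 and the primary outcome. Switching the primary outcome to the Short IBDQ so that it matches the calculation is not advisable: the trial is registered, the IBDQ is named as primary throughout, and the short form is not among the listed instruments.

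The cost is one rewritten paragraph and a larger, less favourable stated detectable difference.
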